### Randomisation and allocation

Following a physical screening examination, volunteers who meet the inclusion criteria will be accepted as participants and undergo baseline assessment at the University of Melbourne. Following baseline assessment, participants will be stratified by treatment site and randomly assigned in permuted block of six and eight to either physiotherapy or placebo treatment groups. The randomisation sequence will be generated using a computer-generated table of random numbers by the study biostatistician (AF). Allocations will be sealed in opaque and consecutively numbered envelopes kept in a locked location. These will be opened in sequence by an independent administrator not involved in eligibility assessment, outcome assessment or treatment. Allocation will be revealed to the treating physiotherapist by fax before the participant presents for treatment.

### Interventions

Ten musculoskeletal physiotherapists located around metropolitan Melbourne will implement both interventions. All treatments will be individual sessions lasting 30–45 minutes, twice weekly for the first 2 weeks, once a week for the next 4 weeks, then once a fortnight in the last 4 weeks (a total of 10 treatments). Participants will be requested to refrain from seeking other forms of treatment during the trial. However, due to ethical considerations, analgesia will be permitted. Use of medications and other therapies will be recorded in a logbook.

The treatments will be standardized and the therapists will be trained to deliver both treatments prior to the study. A comprehensive treatment manual will be produced and the importance of following the protocol emphasised. For the physiotherapy treatment, it is considered important to allow the therapists to adjust the intensity of the standardised treatment techniques to match the participants' capabilities. Thus the number of repetitions of the exercises can be reduced. Deletion of techniques will be permitted if participants find them too painful. At the end of each treatment session for each participant, the physiotherapist will complete a checklist to ensure compliance with the standard approach.

All participants will be requested not to seek other forms of treatment during the study but use of analgesia will be permitted and recorded in a log-book.

#### Physiotherapy intervention group

A standardized treatment protocol has been devised (SC) based on the literature and on the results of a formal written survey we conducted involving 10 musculoskeletal physiotherapists around Australia, considered by the profession to be experts in treating shoulder conditions. These physiotherapists were asked to indicate which of a series of interventions they would generally use at three stages of a 10-week program when managing a typical patient with CRCP. The results showed that the most commonly employed modalities were scapular retraining (100%), rotator cuff exercises (100%), spinal (83%) and shoulder joint mobilisation (50%), soft tissue massage (66%) and taping (50%). Less emphasis is placed on electrotherapy modalities (33%) with few using these, particularly past the first three weeks of treatment ([name] et al unpublished data).

The aims of the resultant physiotherapy intervention are to i) decrease pain; ii) improve functional range of shoulder motion; iii) improve scapular control; iv) strengthen scapular stabilisers and rotator cuff muscles; v) improve posture and thoracic extension range of motion; vi) regain normal shoulder biomechanics. The treatment has five components comprising soft tissue massage, passive mobilisation of the glenohumeral joint, scapula retraining, spinal mobilisation, and home exercises (Table 1). Cognitive behavioural strategies will also be incorporated including education, goal-setting, motivation and positive reinforcement.

**Table 1 T1:** Components of the physiotherapy intervention

**Treatment component**	**Dosage**
Soft tissue massage	6 mins each position
Anterior and posterior shoulder tissues performed in supine and sidelying respectively	
Glenohumeral joint mobilisation	4 × 30 seconds each position
Anteroposterior and inferior joint glides in supine with shoulder at 45° and 90° abduction respectively	
Thoracic spine mobilisation (T1-8)	Grade IV on each level – 4 mins in total
Performed in prone using a central posteroanterior technique	
Cervical spine mobilisation (C5-7)	Grade IV on each level – 4 mins in total
Performed in prone using unilateral posteroanterior technique on both sides	
Scapular retraining	Weeks 1 and 2 only
In sidelying, therapist passively moves shoulder through range from elevation/protraction to retraction/depression then assisted by participant then independently. Isometric holds in retraction/depression	15 reps × 5 reps with 10 sec holds
Postural taping	Continuous (day and night) for two weeks
Taping of the shoulders and scapula to encourage scapular retraction and depression and thoracic extension	Re-applied after one week by the therapist
Exercises	Home program:
Supervised and performed as home program	Twice daily in first two weeks
	Once a day thereafter

##### Soft tissue massage

Deep massage of the soft tissue structures around the shoulder joint will be performed for six minutes in two positions. The posterior joint capsule and scapular shoulder musculature will be massaged in sidelying while the anterior shoulder structures including the supraspinatus, long head of biceps and pectoralis minor tendons will be massaged in supine.

##### Glenohumeral joint mobilisation

Anteroposterior and inferior glenohumeral joint mobilisations will be performed with the participant in supine and with the shoulder in 45 degrees abduction and 90 degrees abduction respectively [35]. Grade IV oscillations (into 50% resistance) will be maintained for 30 seconds and repeated four times.

##### Scapular retraining

The aim of scapular retraining is to improve control of scapular movement, particularly to avoid excessive elevation and protraction, so as to optimise the functional position of the shoulder. The therapist will passively guide the participant from a neutral shoulder girdle posture to an adducted, depressed position, then to an upwardly rotated, elevated position. The participant will then perform the movement actively for several repetitions followed by a 10 second hold in the adducted, depressed posture. This will be repeated 5 times. Postural taping will also be worn full time for the first two weeks. The therapist will firstly apply a protective skin barrier followed by non-rigid, hypoallergenic tape to provide skin protection, and then rigid strapping tape for postural adjustments. The shoulder taping technique aims to encourage a retracted, depressed scapular 
posture and thoracic extension.

##### Spinal joint mobilisations

Mobilisation techniques will be performed to improve range of cervical and thoracic motion, particularly thoracic extension. They will include unilateral lower cervical spine (C5-7) and central upper-mid thoracic spine (T1-8) posteroanterior mobilisation techniques with the participant in prone lying [35]. The therapist will use a Grade IV force at each level, on both sides for the cervical spine and centrally for the thoracic spine. The duration of this treatment will be four minutes for each technique.

##### Home exercises

These are predominantly designed to increase rotator cuff and scapular muscle strength (Table 2). Most exercises require the participant to incorporate their scapular retraining with strengthening of the rotator cuff muscles. Some exercises reinforce and facilitate correct posture. These exercises will be taught and performed during each treatment session and exercise progressions will be introduced regularly throughout the course of the treatment program. Resistance for specific exercises will be provided by hand weights or elastic theraband. Participants will be asked to perform the exercises daily, except during the first week of treatment where exercises will be completed twice per day. Compliance will be monitored via a weekly log book completed by the participant. During the follow-up, the physiotherapy group will be requested to continue daily home exercises.

**Table 2 T2:** Description of specific exercises

**Name**	**Description**	**Dosage**	**Weeks performed**
Scapular setting	Sitting, isometric hold of scapula in retracted and depressed position	5 sec hold × 5 reps	Week 1 then maintained in all exercises
Self-resisted isometric ER	Standing sideways to wall. Upper arm squeezing a towel roll against body, elbow bent with forearm pushing into wall	5 sec hold × 5 reps	Weeks 1&2
Active ER	Sitting with shoulder in 45° Abd resting elbow and forearm on table in IR. Taking shoulder into ER	10 reps × 2	Week 1&2
Shoulder shrugs	Standing with arms slightly abducted and actively elevating scapula then lowering slowly	10 reps × 2 handweight	Week 1&2
Pectoralis minor stretch	Supine with arms in 45° Abd and elbows bent to 90°. Shoulders rotate into ER to stretch muscle	5 reps with 10 sec hold × 2	Weeks 2–6
Wall push up	Standing arms length from wall, hands at shoulder height and shoulders in 45° Abd. Body lowered to wall and then pushed away	5 reps × 2	Weeks 2–10
Chin tuck	Standing with head and back against a wall. Chin tucked in toward neck	5 reps × 10 sec holds	Week 2
Resisted external rotation	Sidelying with affected shoulder uppermost, elbow bent to 90° and holding weight in hand. Weight lifted up toward ceiling with upper arm against body	10 reps × 2 using hand weight	Week 2
Thoracic extension over towel	Supine on a firm surface with arms by side and lying on towel roll placed horizontally on floor at level of maximum thoracic curve	1–3 mins hold	Weeks 3–6
Resisted scapular setting – elbow extension with shoulder neutral	Standing, arm by side and elbow bent holding theraband attached in front at shoulder height. Elbow straightened and slowly flexed whilst keeping scapula in set position	10 reps × 2 using theraband	Weeks 3–6
Resisted external rotation	Standing, elbow bent to 90° and forearm along stomach and holding onto theraband at waist height. Keeping elbow in to side, pulling against theraband to perform ER	10 reps × 2 using theraband	Weeks 3&4
Resisted internal rotation	Standing, elbow bent to 90° and shoulder in ER and holding onto theraband at waist height. Keeping elbow in by side, pulling against theraband to perform IR	10 reps × 2 using theraband	Weeks 3&4
Resisted horizontal row	Standing, both arms outstretched holding onto theraband attached at waist height. Both arms pulled back toward trunk with elbows flexed	10 reps × 2 using theraband	Weeks 3–10
Resisted external rotation in supported 90° Abd	Sitting with shoulder supported in 90° Abd on table and forearm resting on table holding a weight in hand. Weight lifted toward ceiling keeping elbow on table	10 reps × 2 using hand weight	Weeks 5&6
Resisted internal rotation in supported 90° Abd	Sitting with shoulder supported in 90° Abd on table and forearm resting on table holding theraband attached behind. Hand taken to table to perform IR	10 reps × 2 using theraband	Weeks 5&6
Corner stretch	Standing with one hand on each corner wall at shoulder height and elbows bent. Leaning in toward corner to stretch anterior shoulder and thoracic spine	5 reps × 10 sec holds	Weeks 5–10
Resisted scapular setting – elbow flexion	Standing with hands at chest height, elbows bent and holding onto theraband which is then stretched apart by trying to straighten both elbows	10 reps × 2	Weeks 7–10
Resisted external rotation in unsupported Abd	ER performed in standing with shoulder unsupported in 45° scapular plane, elbow bent and holding theraband attached in front	10 reps × 2	Weeks 7–10
Resisted internal rotation in unsupported Abd	IR performed in standing with shoulder unsupported in 45° scapular plane, elbow bent and holding theraband attached behind	10 reps × 2	Weeks 7–10

ER = external rotation; IR = internal rotation; Abd = abduction

#### Placebo group

As for many procedural interventions, it is difficult to design a placebo treatment that fully mimics a physiotherapy program. However, our aim is to control for the effect of regular contact with a therapist, the belief that treatment will assist CRCP and the therapeutic environment. Participants in the placebo group will receive the same number and length of visits as those in the physiotherapy group but will receive only sham ultrasound and light application of a non-therapeutic gel. Participants in the placebo group will receive no instruction in exercise techniques and no manual therapy. We have used an identical placebo protocol in completed clinical trials of physiotherapy for patellofemoral pain syndrome [36], knee osteoarthritis [37] and shoulder adhesive capsulitis [38]. In these trials, between 68% to 83% of participants in the placebo group thought they had received 'real' physiotherapy or were unsure. Blinding index was 0.49 (bootstrap 95% CI 0.40 to 0.56), interpreted as moderate success of blinding in one study [38]. The placebo participants will not receive any intervention or complete any home exercises during the 12 week follow-up period.

### Blinding

To maintain blinding, the plain language statement and consent procedures will inform participants that they have an equal chance of receiving real or placebo physiotherapy but will not disclose details of the actual treatments. A blinded examiner will perform all outcome assessments. Participant blinding will be optimised by using a realistic placebo intervention and by ensuring participants do not attend for treatments or assessments concurrently. Participants will also be requested to refrain from discussing their treatment with the outcome assessor. At trial completion, participants will nominate which group they believed they have been allocated to. The data manager and statistician will be unaware of treatment allocation until completion of analyses.

### Outcome assessment

Demographic information will be collected including age, sex, duration of symptoms, previous investigations and treatment, history of medical conditions, and medication use. Expectation of a beneficial treatment effect will be scored on an ordinal scale from 1 to 5 with higher scores indicating higher expectations.

A number of outcome measures will be collected for this study (Table 3). A combined shoulder pain and disability index (SPADI) will be used to measure changes in shoulder pain and function at final and follow-up time points. This is a self-administered, shoulder-specific index consisting of 13 items divided into two subscales: pain (five items) and disability (eight items) [39]. Responses to each item are recorded on a 11 point Likert scale where 0 = "no pain" or "no difficulty" and 10 = "worst imaginable pain" or "so difficult it required help" for the pain and disability items respectively. The SPADI score is calculated by summing then averaging the two subscales to give a score out of 100 (higher score more pain/disability). It has acceptable test-retest reliability, construct validity and responsiveness [39-41]. We have confirmed the clinimetric properties of this index and found it to be more responsive than other shoulder-specific questionnaires (effect sizes 1.01–1.69) ([name] et al unpublished data).

**Table 3 T3:** Outcome measures

**Primary Outcomes**	**Measurement**
Shoulder pain and disability index (SPADI)	13 items scored on an 11 point Likert scale
Average pain over past week	11 point horizontal numeric rating scale (end descriptors of 0 = no pain and 10 = worst pain possible)
Participant perceived global rating of change overall	Ordinal scale (1-much worse, 2-slightly worse, 3-no change, 4-slightly better, 5-much better)

**Secondary Outcomes**	

Worst pain, and pain on 3 self selected activities in past week	11 point horizontal numeric rating scale (end descriptors of 0 = no pain and 10 = worst pain possible)
Amount of stiffness, weakness, and interference to activities of daily living in past week	11 point horizontal numeric rating scale
Participant perceived global rating of change in pain, strength, and stiffness	Ordinal scale (1-much worse, 2-slightly worse, 3-no change, 4-slightly better, 5-much better)
Health-related quality of life	• SF-36 • Assessment of Quality of Life index (AQol)
Isometric muscle strength of shoulder abduction, internal rotation and external rotation	Hand held dynamometer

**Other measures**	

Compliance	• Number of therapy visits • Physiotherapy group: Completion of home exercises via log-book
Adverse effects	Log-book and open probe questionning

Average pain, worst pain and pain on three self-selected activities (over the past week) will be measured by separate 11-point numeric rating scales [12] numbered in 1 cm intervals. The amount of weakness, stiffness and interference with activities of daily living (over the past week) will be measured similarly.

Participant perceived global rating of change overall and in pain, strength, and stiffness (since commencement) will be recorded on separate 5 point Likert scales (1-much worse, 2-slightly worse, 3-no change, 4-slightly better, 5-much better). Measuring participant perceived improvement using a rating of change scale has been shown to be a clinically relevant and stable concept for interpreting truly meaningful improvements from the individual perspective [42]. A successful outcome will be defined a priori as 'much better' on the rating scale.

Health-related quality of life will be measured using the Medical Outcomes Study 36-item short form (SF-36) (8 subscales scaled from 0–100 where a higher score represents better health) [43]. This the most widely used generic measure of health related quality of life and permits comparison of the impact of disease and treatment across studies and populations. The clinimetric properties of the SF-36 have been well established on samples from diverse populations [43,44]. We will also use the Assessment of Quality of Life (AQoL) instrument. The AQoL comprises 15 items on ordinal scales with four levels per item covering five dimensions (illness, independent living, social relationships, physical senses and psychological wellbeing). It produces a single utility index that ranges from -0.04 (worst possible health-related quality of life) to 1.00 (full health-related quality of life). The AQoL has strong psychometric properties [45,46]. The AQoL can also be converted into a utility index to calculate quality adjusted life years (QALY).

Isometric shoulder strength for shoulder abduction, internal and external rotation will be measured using the Nicholas Manual Muscle tester (Lafayette, USA). For shoulder abduction, participants will be positioned in supine with the shoulder in 90 degrees of abduction and the elbow flexed to 90 degrees. The dynamometer will be positioned on the lateral surface of the distal humerus, proximal to the lateral epicondyle. Measurements of external and internal rotation will be performed in sitting with the arm by the side against a folded towel, the elbow flexed to 90 degrees and the forearm in midprone. The dynamometer will be positioned on the distal forearm. One warm up trial followed by three maximal contractions will be performed and the median reading taken. We previously measured 12 people with CRCP on two occasions three days apart. Intraclass correlation coefficient (ICC 2,3) values were 0.95 for abduction, 0.96 for internal rotation and 0.93 for external rotation indicating that test retest reliability was excellent.

A number of other measures will be obtained (Table 3). Participant compliance will be obtained by recording the number of physiotherapy sessions attended (out of a maximum number of 10). Those in the physiotherapy group will complete a daily log-book to record the number of home exercise sessions completed. Adverse events and the use of co-intervention will be recorded in a log-book and by open-probe questioning by the assessor at trial completion. Log-books will be posted back to the assessor on a monthly basis and checked for completion. At the final and followup measurement time points, study participants will be asked to indicate which treatment they believe they have received and reasons for that choice to assess the success of blinding.

Information on direct health care costs, direct non-health care costs and production losses over the 22 weeks will be collected by a logbook posted back to the assessor on a monthly basis and checked for completion. Direct health care costs will include costs of physiotherapy attendance (assumed zero in the placebo group), additional health provider visits, tests, prescription and over the counter medication, professional home care and hospitalisation. These will be valued using published prices for medical costs. Direct non-health care resources will include use of paid and unpaid help, lost time and travel, and number of lost days at work.

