**Methods/Design:**

This randomised, double-blind, placebo-controlled trial will involve 200 participants with CRCP recruited from medical practices, outpatient departments and the community via print and radio media. Participants will be randomly allocated to a physiotherapy or placebo group using concealed allocation stratified by treating physiotherapist. Both groups will receive 10 sessions of individual standardised treatment over 10 weeks from one of 10 project physiotherapists. For the following 12 weeks, the physiotherapy group will continue a home exercise program and the placebo group will receive no treatment. The physiotherapy program will comprise shoulder joint and spinal mobilisation, soft tissue massage, postural taping, and home exercises for scapular control, posture and rotator cuff strengthening. The placebo group will receive inactive ultrasound and gentle application of an inert gel over the shoulder region. Blinded assessment will be conducted at baseline and at 10 weeks and 22 weeks after randomisation. The primary outcome measures are self reported questionnaires including the shoulder pain and disability index (SPADI), average pain on an 11-point numeric rating scale and participant perceived global rating of change. Secondary measures include Medical Outcomes Study 36-item short form (SF-36), Assessment of Quality of Life index, numeric rating scales for shoulder pain and stiffness, participant perceived rating of change for pain, strength and stiffness, and manual muscle testing for shoulder strength using a handheld dynamometer. To evaluate cost-effectiveness, participants will record the use of all health-related treatments in a log-book returned to the assessor monthly. To test the effect of the intervention using an intention-to-treat analysis, linear regression modelling will be applied adjusting for baseline outcome values and other demographic characteristics. Participant measures of perceived change will be compared between groups by calculating the relative risks and their 95% confidence intervals at each time point using log binomial regression.

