## Methods/Design

### Design

This will be a randomised placebo controlled trial with blinded participants and outcome assessors (Figure 1). The trial comprises a 10-week intervention and a 12-week follow-up (Figure 1). Participants will be assessed immediately before treatment (baseline), immediately after treatment (final) and at 22 weeks (follow-up) post randomisation. The assessments will be performed by the same assessor who will be blind to group allocation.

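### Log-books go monthly to the blinded outcome assessor, with no exception for the home-exercise log-book that only the physiotherapy group keeps

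*Protocol article*

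**What the plan says.** All references are to the protocol article.

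- **Assessor blinding.** The Design section says "The assessments will be performed by the same assessor who will be blind to group allocation". The Blinding section adds "A blinded examiner will perform all outcome assessments". To protect this, participants are asked not to talk about their treatment: "Participants will also be requested to refrain from discussing their treatment with the outcome assessor".
- **Who keeps an exercise record.** The Outcome assessment section says "Those in the physiotherapy group will complete a daily log-book to record the number of home exercise sessions completed". Table 3 agrees: "Physiotherapy group: Completion of home exercises via log-book". The Placebo group section says "Participants in the placebo group will receive no instruction in exercise techniques and no manual therapy" and rules out home exercises in the 12-week follow-up. The physiotherapy group is asked to continue daily exercises in that period.
- **Where the log-books go.** After a sentence on adverse events and co-interventions, the Outcome assessment section says "Log-books will be posted back to the assessor on a monthly basis and checked for completion". The paragraph on costs repeats the monthly return to the assessor, and so does the abstract: "participants will record the use of all health-related treatments in a log-book returned to the assessor monthly".
- **Other contact with the assessor.** The assessor questions participants about adverse events and co-interventions at trial completion. At both post-baseline time points, participants state which treatment they think they had and why. Who collects that answer is not stated.

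**The concern.** An entry recording home exercise can come only from the physiotherapy arm. If such records are posted to the person who is meant to be blind, that person can learn the allocation before measuring the outcome. The one stated safeguard for the participant's contact with the assessor covers conversation and does not cover paper.

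At stake are the outcomes that pass through the assessor's hands. Isometric strength in three directions is tested with a hand-held dynamometer, where the tester's handling and encouragement can matter. The test-retest coefficients given for this device (0.93 to 0.96, in 12 people) show repeatability. They do not show resistance to knowledge of the arm. Open questioning on adverse events and co-interventions can also be shaped by what the questioner knows. The blinding check that is described uses the participants' own guesses, so it would not detect an unblinded assessor.

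**Working it through.** No sample-size, power or error-rate figure bears on this point. The check sets the statements side by side and counts the returns.

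**1. Does an exercise record identify the arm?** Physiotherapy participants exercise at home through the 10 treatment weeks and the 12 follow-up weeks. Placebo participants have no exercise instruction during treatment and no home exercises in follow-up. An exercise record therefore identifies the arm in both periods.

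**2. Does that record reach the assessor?** The posting sentence uses the plural for log-books without qualification. It comes two sentences after the one that introduces the exercise log-book, and no other destination is given for any log-book. Two arrangements are possible:
- One common book: the exercise entries travel with the adverse-event, co-intervention and cost entries.
- Separate books: only physiotherapy participants have an exercise book to post, so its arrival is informative even if unopened.

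Under either arrangement, receipt can reveal the arm.

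**3. Is this the same assessor?** The sentence before the posting sentence has the assessor questioning participants. The Design section describes one assessor for all assessments, and no second assessor is mentioned.

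**4. How many returns come before each assessment?** Inputs: monthly return, with assessments at weeks 10 and 22. Return k falls at week k × m, where m is the length of a month in weeks.

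| Return | m = 4 | m = 4.35 |
|---|---|---|
| 1 | week 4 | week 4.35 |
| 2 | week 8 | week 8.70 |
| 3 | week 12 | week 13.05 |
| 4 | week 16 | week 17.40 |
| 5 | week 20 | week 21.75 |

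Under both definitions, 2 returns fall before week 10 and 5 by about week 22. With a calendar month, the fifth falls so close to week 22 that postal delay could bring it after the visit. These counts show opportunity for exposure. They do not measure bias.

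**5. Which outcomes depend on the assessor?** The three primary outcomes (SPADI, average pain, global rating of change) are reported by the participant, and SPADI is described as self-administered. Dynamometer strength is measured by the assessor and is secondary.

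**The case against.** The strongest reply is that the article never says there is only one book. The Home exercises section speaks of a weekly log for compliance. The Outcome assessment section speaks of a daily exercise log, then of a log-book for adverse events and co-interventions, then of one for costs. The exercise log may be separate and may go elsewhere under a fuller document. This stands as a limit on certainty. It does not remove the contradiction, because the text as written sends log-books to the assessor without exception, and a separate book posted by one arm is itself revealing.

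Three narrower objections also stand:
- The check for completion is worded without naming who does it. Receipt by the assessor is stated; reading by the assessor is an inference.
- The abstract sentence concerns only use of health-related treatments, which both arms record. It confirms the destination but does not by itself show disclosure of allocation.
- Questioning on adverse events and co-interventions is already set at trial completion, so it cannot affect the week-10 assessment. A participant's guess is also not disclosure of allocation, since participants are meant to be blind. In earlier trials with the same placebo, 68% to 83% of placebo participants thought they had real treatment or were unsure. The stated reasons could still be informative if the assessor saw them before week 22.

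A reader might go further and infer that allocation is disclosed for essentially every participant who returns a log-book, so that assessor blinding fails outright. The article does not support that. It would require that exercise records are in the returned post and that the assessor notices them, and a protocol cannot show what happened in practice.

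**Conclusion.** The concern holds as a contradiction in the written procedure: the routing of log-books cannot be squared with a single blinded assessor unless the exercise record is excepted, and it is not. About 2 returns per participant would precede the week-10 assessment and about 5 would arrive by about week 22. This assumes that the unqualified plural includes the exercise log-book and that the assessor who receives the post is the one who measures outcomes. Both are the natural reading.

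The direct risk is confined to the secondary strength outcomes and to adverse-event and co-intervention questioning. A reader might infer that the primary results are compromised. The article does not support this: those outcomes are self-reports, and any effect would have to act indirectly, through how the assessor handles the visit. The sample size and the planned analyses are unaffected. The text is wrong as written and should be corrected, but it does not threaten the main comparison directly.

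**What to change.** 1. Have all log-books, or at least the exercise log-books, posted to and checked by someone with no part in outcome assessment. The independent administrator named under Randomisation and allocation is suitable: that person already opens the allocation envelopes, so nobody new is unblinded.
2. Correct the abstract and both log-book statements in the Outcome assessment section to match. This should be done before the first returns, because an assessor who has seen an exercise record cannot be blinded again.
3. Have participants complete the week-10 treatment guess and reasons themselves, after the strength tests, and seal the form from the assessor.
4. Leave the open questioning on adverse events and co-interventions with the assessor, and state that it follows all week-22 measurements. It should not pass to the administrator, who knows every allocation and would be a definitely unblinded questioner.

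The cost is clerical. At one book per return, 5 returns × 200 participants gives up to 1,000 log-books to receive and check. Re-routing only a separate exercise book would give up to 5 × 100 = 500. The article gives the administrator no task beyond opening envelopes, so this is added work, though modest.
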